**Primary outcome**						
	CGM^a^ adherence (optimizer vs subuser)	OMNIdiasense score	✓	✓	✓	✓
	Sensor-wear days/week	CGM device records	✓	✓	✓	✓
	MI^b^-guided behavior change consultation	Session log	✓		✓	✓

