### Substudy 3: Pilot Evaluation of OMNIdiasense

#### Design

Substudy 3 evaluates the AI-assisted assessment tool OMNIdiasense through 2 parallel components, both fed by an embedded AI model-development workstream described below.

Quasi-experimental single-arm pilot: 100 existing CGM subusers identified in substudy 2 receive OMNIdiasense assessment prior to CGM reintroduction, followed by MI-guided behavioral support delivered by a trained diabetic nurse within the routine pediatrics endocrine clinics.Pilot RCT: 50 newly recruited children with T1DM, randomized 1:1 to (1) intervention, OMNIdiasense assessment plus MI-guided support before CGM initiation or (2) usual care without exposure to the tool. Both arms receive CGM and standard clinical follow-up.

All 150 participants are followed for 12 months, with assessments at baseline, 3, 6, and 12 months. The flow of participants is presented in Figure 1.

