#### Outcomes

The primary outcome is the between-group difference in CGM adherence, defined as mean days per week of sensor wear over the 12-month follow-up. The CGM adherence outcome will be measured from pharmacy dispensing records, self-report, and clinical records. Differences between device types will be recorded, and significant findings across different devices will be analyzed.

Key secondary outcomes are change in HbA_1c_, time in range, anthropometric measures (weight and BMI), blood pressure, lipid panel, RFT, LFT, drug/treatment changes, OMNIdiasense risk score change, barriers and facilitators of CGM use, and patient satisfaction (Multimedia Appendix 9). Table 2 shows the full schedule of assessments.

**Table 2 table2:** Schedule of assessments in substudy 3.

Variable		Tool/source	Baseline	3 months	6 months	12 months

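### Table 2 sources the primary-outcome row for optimizer/subuser status from the tool's own prediction, and the text's list of wear sources leaves out the device records that the table schedules

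*Protocol article*

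**What the plan says.** **Table 2 (schedule of assessments in substudy 3), primary-outcome block.** Two rows concern adherence, both ticked at baseline, 3, 6 and 12 months:

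- CGM "adherence (optimizer vs subuser"), with "OMNIdiasense score" as tool/source.
- "Sensor-wear days/week", with "CGM device records" as tool/source.

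**Substudy 3, Outcomes.** The primary outcome is the between-group difference in CGM adherence, "defined as mean days per week of sensor wear over the 12-month follow-up". On sources: "The CGM adherence outcome will be measured from pharmacy dispensing records, self-report, and clinical records". The same section lists "OMNIdiasense risk score change" among the key secondary outcomes.

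**Substudy 3, Design.** The RCT intervention arm has the OMNIdiasense assessment and motivational interviewing (MI) before starting CGM. The control arm has "usual care without exposure to the tool".

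**Other places that bear on the point.**

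- The section on how the score will be used describes it as a per-child probability of turning into a subuser.
- The Intervention section has nurses feed the score back in the MI sessions.
- Substudy 2, Design and Population, defines optimizers and subusers by observed wear: at least 6 days a week, against fewer than 6 or discontinued.
- Randomization and Blinding blinds outcome assessors and the analyst, but not participants or those delivering the intervention.

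**The concern.** An outcome row should name an instrument that observes the outcome. Here the binary adherence row names a forecast of it, and that forecast is one of the two components of the intervention. Read literally, the row would record whether the model expects a child to be a subuser, not whether the child wore the sensor.

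The quantity that the text does define properly, days per week of wear, has two source lists that do not agree. The one in Outcomes lets self-report in and leaves device records out. Families know their allocation, and those in the intervention arm have had nurse-led sessions about wearing the sensor, so self-report is the source most open to a difference in reporting between arms.

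Table 1 says the pilot RCT is to supply the effect size for a definitive multicenter trial. A primary measure that is circular, available in one arm only, or open to differential reporting would carry its fault into that trial's planning.

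**Working it through.** The protocol states no figure that this point could reproduce, so the check is a comparison of the passages.

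**Step 1: is the score a measure of status?**

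| Place | What it says about the score or the status |
|---|---|
| Table 2, first primary row | The score is the tool for optimizer/subuser status |
| How the score will be used | The score is a predicted probability of future subuser status |
| Substudy 2, Design and Population | Status is fixed by observed days per week |
| Outcomes | Score change is a secondary outcome |
| Design; Intervention | The score is produced and fed back as part of the intervention |

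The first row conflicts with the other four. The stated objective is also to forecast adherence before a device is dispensed, whereas Table 2 uses the score as a reading of adherence at 3, 6 and 12 months, when actual wear can be observed.

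**Step 2: could the score move without wear moving?** The prespecified core predictors include the CGM benefit and burden scales and the self-efficacy scale. The MI sessions work on the pros and cons of CGM and on self-efficacy. If those scales are re-administered to update the score (Table 2 has no row for them), MI could improve the score with no change in sensor use. This is a conditional argument, but it shows why a prediction is a poor stand-in for the behaviour.

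**Step 3: what contrast does the row give in the RCT?** Table 2 has no columns by arm, so there are two readings:

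- *Controls are not scored.* This is the plain inference from having no exposure to the tool. The row then has values for the 25 intervention children and none for the 25 controls, so it offers no between-group comparison. The secondary outcome of score change has the same gap.
- *Controls are scored in the background without disclosure.* A comparison then exists, but of predictions rather than of wear.

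Neither reading gives a between-group comparison of observed status.

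**Step 4: which sources feed days per week?**

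| Source | Outcomes text | Table 2, wear row |
|---|---|---|
| Device records | not named | named |
| Pharmacy dispensing | named | not named |
| Clinical records | named | not named |
| Self-report | named | not named |

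The two lists have no entry in common. Dispensing shows supply rather than wear. Self-report comes from unblinded families, and blinding the assessor does not alter what a family reports. The source closest to wear is already scheduled at every visit, but it is absent from the text that defines the outcome.

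**Step 5: is the binary row idle?** No. The substudy 3 sample-size paragraph is built on the prevalence of optimal use (about 50%) and an odds ratio (0.53), and Data Analysis lists chi-square tests for the RCT. The binary status therefore has a role in the plan and needs a valid source.

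**The case against.** The strongest reply is that the primary outcome is defined correctly in the text as average weekly wear, and that Table 2's second row measures that variable from device records at every visit. The primary block also contains a row for the MI consultation taken from a session log, which is not an outcome at all. The block looks like a loose schedule, and a mislabelled source cell is at least as likely as a plan to replace wear with a prediction. This stands. It limits the point to an inconsistency and does not show that the trial lacks a wear-based primary outcome.

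Three stronger readings are tempting and are not supported:

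- *The primary outcome is missing for the whole control arm.* The documents say only that controls are not exposed to the tool. They do not say that no score is computed, and scores are kept in the research database rather than the clinical record. In any case the wear-based outcome exists for both arms.
- *The baseline wear tick is impossible.* RCT children have not yet received CGM, so the tick cannot apply to them. But Table 2 also covers the 100 existing subusers in the single-arm component, whose within-person change needs a baseline. A footnote is enough.
- *The resulting bias can be put in numbers.* The protocol gives no accuracy for the score, no SD for days per week and no rate of over-reporting. Dilution from misclassifying status would also need scores in both arms, so it cannot be added to the case where controls have none.

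It can also be said that the order of precedence among sources is normally left to the statistical analysis plan, which is available on request but not shown, and that clinical records might include device downloads. That is fair on precedence. It does not remove the disagreement between the Outcomes text and Table 2 over which sources are used.

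**Conclusion.** The point holds as an internal inconsistency in how the primary outcome is measured. One of Table 2's two adherence rows names a prediction, which is itself part of the intervention, as the instrument for a status that the protocol defines by observed wear. On either reading of the control arm, that row does not compare observed adherence between groups. Separately, the text's sound days-per-week outcome is tied to sources that omit the scheduled device records and admit self-report from unblinded families.

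The reach is the binary adherence row at all four visits, the secondary score-change comparison in the 50 RCT children, and the source of the main wear measure. No numerical bias is claimed. The conclusion rests on the documents' wording alone; the only inference is that controls may have no score, and the defect remains if they do. It should be corrected before pilot recruitment, planned for the fourth quarter of 2026.

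**What to change.** - **Table 2, first primary row:** replace the score as tool/source with status derived from observed days per week in CGM device records, using the cut-off already defined for substudy 2.
- **Outcomes text:** name device records as the primary source in both arms. Allow dispensing or clinical records as a fallback under one stated rule applied identically to both arms, and use self-report only in a sensitivity analysis.
- **Risk score:** keep its change as a secondary measure, descriptive within the intervention arm, unless a masked score is computed for controls. If it is, say so.
- **Table 2 footnote:** baseline wear applies only to the single-arm component.

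The cost is a wording change to one table and one paragraph, since device records are already scheduled at every visit. The small downside is that some device uploads will be missing, and the fallback rule will have to cover them.

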**Secondary outcomes**						
	Demographic characteristics	Study questionnaire	✓			
	Medical history of T1DM^c^	Study questionnaire	✓			
	Family history of diabetes	Study questionnaire	✓			
	Comorbidities	Study questionnaire	✓			
	Drug/treatment history	Health records	✓		✓	✓
	Anthropometrics (weight, BMI)	Health records	✓		✓	✓
	Blood pressure	Health records	✓		✓	✓
	Cholesterol, RFT^d^, LFT^e^	Health records	✓		✓	✓
	HbA_1c_^f^	Health records	✓		✓	✓
	Barriers and facilitators	Open-ended interview	✓		✓	✓
	Patient satisfaction	Satisfaction questionnaire			✓	✓
	Staff satisfaction (exit survey)	Satisfaction questionnaire				✓

^a^CGM: continuous glucose monitoring.

^b^MI: motivational interviewing.

^c^T1DM: type 1 diabetes mellitus.

^d^RFT: renal function test.

^e^LFT: liver function test.

^f^HbA_1c_: hemoglobin A_1c_.

#### Randomization and Blinding

In the RCT component, computer-generated 1:1 simple randomization will be performed centrally by an independent statistician. Allocation concealment will use sequentially numbered, opaque, sealed envelopes opened only after enrollment confirmation. Outcome assessors and the data analyst will be blinded to allocation; participants and intervention deliverers will not be blinded owing to the nature of the intervention.

#### Data Analysis

Analyses will follow the intention-to-treat principle. Descriptive statistics will summarize baseline characteristics. Within-person change in the quasi-experimental arm will be analyzed with paired *t* tests, Wilcoxon signed-rank tests, or generalized estimating equations as appropriate. Between-group differences in the RCT will use *t* tests, chi-square tests, and mixed effects models with random intercepts for repeated measures. Multivariable linear and logistic regressions will explore predictors of adherence change. Missing data will be handled by multiple imputation under a missing-at-random assumption with sensitivity analyses. Prespecified subgroup analyses will examine age band (10-13 vs 14-18 years), sex, governorate (Muscat vs others), and insulin modality (multiple daily injections vs pump); any post hoc subgroup analyses will be flagged as exploratory. The pilot RCT report will follow the CONSORT (Consolidated Standards of Reporting Trials) 2025 extension for pilot and feasibility trials, and the interventional protocol adheres to SPIRIT (Standard Protocol Items: Recommendations for Interventional Trials)-AI 2025 (Multimedia Appendix 10).

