#### Inclusion and Exclusion Criteria

Quasi-experimental component: existing children with T1DM aged 10-18 years classified as CGM subusers in substudy 2; primary caregiver consents and child assents.

RCT component: newly diagnosed children with T1DM, aged 10-18 years, eligible for CGM under the national program, who have not yet received CGM. Exclusion: severe psychiatric or cognitive comorbidity precluding informed assent or interview participation.

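### The RCT's HbA1c comparison names t tests and random-intercept models but states no baseline adjustment; adjusting would gain precision at no cost

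*Protocol article*

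**What the plan says.** Substudy 3, Outcomes: "Key secondary outcomes are change in HbA_1c_, time in range" and a list of further measures that includes weight, BMI, blood pressure and laboratory values. Table 2 schedules HbA1c and these other measures at baseline, 6 months and 12 months.

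Substudy 3, Data Analysis: RCT between-group differences use t tests, "chi-square tests, and mixed effects models with random intercepts for repeated measures". The methods are listed together and not assigned to outcomes. No baseline covariate is named. The only regressions with covariates in that section are exploratory models for predictors of adherence change.

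Substudy 3, Design and Randomization and Blinding: "50 newly recruited children with T1DM, randomized 1:1 to" the two arms, and "computer-generated 1:1 simple randomization will be performed centrally by an independent statistician". No stratification is stated.

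Inclusion and Exclusion Criteria: the RCT enrols "newly diagnosed children with T1DM, aged 10-18 years, eligible for CGM under the national program, who have not yet received CGM".

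**The concern.** For an outcome expressed as change, the listed t test would most naturally be run on change scores. A change score subtracts the whole baseline value whatever its relation to the later value, so it carries baseline noise into the comparison unless the regression slope of follow-up on baseline is 1. Simple randomization of 50 children does nothing to limit a chance difference in baseline HbA1c, and the stated analysis does not remove it properly either.

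The mixed model does not solve this as worded. In the usual arm-by-time model with complete data, the 12-month interaction is the difference in mean change, with the sampling variance of a change score.

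At stake is the precision of the clinical secondary estimates. Table 1 counts secondary clinical outcomes among the RCT's outputs and effect-size estimates among its contributions to a definitive trial.

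**Working it through.** The plan gives no precision or power figure for HbA1c, so there is none to reproduce. Its RCT sample-size statement concerns optimal CGM use and is not an input here.

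**Inputs.** From the protocol: 25 children per arm, baseline HbA1c collected, final visit at 12 months. Assumed, because the protocol gives no values: the ratio k of baseline SD to follow-up SD, and the correlation ρ between the two.

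**Formulas** (follow-up SD set to 1, variance per child):
- change score: k² + 1 − 2ρk
- 12-month value alone: 1
- ANCOVA: 1 − ρ²

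Change score minus ANCOVA is (k − ρ)², so the change score is never better and is equal only when k = ρ. Information lost = 1 − (1 − ρ²)/(k² + 1 − 2ρk). With equal SDs (k = 1) this reduces to (1 − ρ)/2.

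**Information lost by a change-score t test against ANCOVA**

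| k | ρ = 0.2 | ρ = 0.5 | ρ = 0.7 |
|---|---|---|---|
| 1 | 40% | 25% | 15% |
| 1.25 | 53% | 43% | 37% |
| 1.5 | 64% | 57% | 56% |
| 2 | 77% | 75% | 77% |

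Example, k = 2 and ρ = 0.5: 0.75/3.00 = 0.25, so 75% is lost and 50 children are worth 12.5. The loss passes 50% only when k exceeds about 1.18 (ρ = 0.2), 1.37 (ρ = 0.5) or 1.41 (ρ = 0.7).

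A t test on 12-month values alone loses ρ²: 4%, 25% and 49% at the same three correlations.

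Estimating the ANCOVA slope costs a factor of about 1 + 1/46, roughly 2%, which does not alter the picture.

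**In HbA1c points** (assumed baseline SD 2.0, 12-month SD 1.5, ρ = 0.3):
- Change: variance 4 + 2.25 − 1.8 = 4.45; SE = √(2 × 4.45/25) = 0.60.
- ANCOVA: variance 2.25 × 0.91 = 2.05; SE = √(2 × 2.05/25) = 0.40.
- Variance ratio 2.17. Detectable difference at 2.8 SE: 1.67 against 1.13 points.
- With equal SDs of 1.5 the ratio is 1.54; with baseline SD 2.5 it is 3.05.

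**Chance imbalance, same assumptions.** SE of the baseline difference between arms: √(2 × 4/25) = 0.57 points. The ANCOVA slope is 0.3 × 1.5/2.0 = 0.225. An imbalance of one SE therefore moves the change-score estimate by 0.57 × (1 − 0.225) = 0.44 points relative to ANCOVA. It moves the unadjusted 12-month comparison by 0.57 × 0.225 = 0.13 points.

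**Random-intercept model with baseline means constrained equal.** The implied slope is 2 × 0.3 × 2.0 × 1.5/(4 + 2.25) = 0.288. The variance is 2.25 + 0.288² × 4 − 2 × 0.288 × 0.9 = 2.063, against 2.048 for ANCOVA: about 99% efficient. More generally it is 98% to 100% efficient for k up to 1.25 and ρ up to 0.5, and 89% at k = 2, ρ = 0.5. Without the constraint, the change-score row of the arithmetic applies.

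**The case against.** The strongest reply is that the protocol never commits HbA1c to an unadjusted t test. The methods are listed for all RCT outcomes at once, and for a measure taken at three visits the mixed model fits by name. Such a model can use the baseline and recover nearly all the loss. Covariates are often left to the statistical analysis plan, which the protocol says exists and which is not shown.

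Much of this stands. A reader might infer that the plan fixes an unadjusted t test for HbA1c; it does not. A reader might also infer that a random-intercept model cannot serve; with baseline means constrained equal, or with baseline as a covariate, it serves well in most of the settings examined. What remains is that the published text names methods for a change outcome, and neither the t test nor the default arm-by-time form of the mixed model adjusts for baseline. The efficient form needs a constraint or covariate that the text does not state. The point is therefore a better method at no cost, rather than a complaint about missing detail.

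Two further inferences are tempting. One is that newly diagnosed children have high and widely spread baseline HbA1c, so that most of the precision is lost. That may be plausible, but the protocol gives no level, SD or correlation, and with equal SDs the loss never exceeds 50% for any non-negative correlation. The other is that the trial as a whole is weakened. The primary outcome is "defined as mean days per week of sensor wear over the 12-month follow-up", and these children have no pre-device wear to adjust for. Future Directions would power the definitive trial on the adherence difference, so the HbA1c estimate is not its stated sizing input.

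**Conclusion.** The point holds for the continuous secondary outcomes with a baseline, HbA1c chief among them. As worded, the analysis permits comparisons less efficient than ANCOVA and more exposed to chance baseline imbalance. The loss for a change-score analysis is about 15% to 40% of the information if the SDs are equal and the correlation lies between 0.7 and 0.2, and about 75% if the baseline SD is double the follow-up SD. These figures rest on assumed SD ratios and correlations; only the direction is free of them. A loss of more than half needs a baseline SD about 1.2 to 1.4 times the follow-up SD or more, which the protocol does not document. The primary adherence comparison is untouched. This is a free improvement, not an error that threatens the trial.

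**What to change.** In Substudy 3, Data Analysis, state that HbA1c and the other continuous secondary outcomes with a baseline are compared between arms at 12 months adjusted for the baseline value. Use either ANCOVA, or a repeated-measures model with baseline as a covariate or with baseline means constrained equal across arms. State that the unadjusted t test is not used for inference on these outcomes. An unstructured covariance is optional. Time in range falls outside this sentence, because children who have not yet received CGM have no pre-device value.

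The cost is a sentence or two. Baseline values are already scheduled, and no visits or participants are added. According to the Results section, substudy 3 recruitment is planned for the fourth quarter of 2026, so the change can be made before enrolment. If the statistical analysis plan already specifies this, the protocol wording need only be brought into line with it.

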#### Handling of Missing Data, Class Imbalance, Overfitting, and Feature Selection

Missingness will be quantified by variable and pattern. Variables with >40% missingness will be excluded unless they carry strong prior clinical value, in which case they will be retained with an explicit missing indicator. Item-level missing data on validated scales will be imputed using each scale’s published rules; remaining missingness will be addressed by multiple imputation by chained equations (m=20) under a missing-at-random assumption, with a tipping-point sensitivity analysis to test robustness against a missing-not-at-random scenario.

Class imbalance between optimizers and subusers will be addressed at 2 levels: stratified sampling during cross-validation to preserve outcome proportions in every fold, and class-weighted loss functions (inverse-frequency weights) for the gradient-boosted, SVM, and neural-network classifiers. Synthetic minority oversampling will be evaluated as a sensitivity analysis only and not as the primary approach, to avoid optimistic generalization.

Overfitting will be controlled through nested cross-validation (outer 5-fold for performance estimation, inner 5-fold for hyperparameter tuning), L1/L2 regularization for linear models, early stopping and shrinkage for boosted trees, and dropout and weight decay for the neural network. The full train-test partition (80/20) will be temporally separated where possible (children enrolled later become the held-out set) to give a more realistic estimate of prospective performance.

Feature selection will use a stability-selection wrapper around L1-penalised logistic regression with 100 subsampled fits; features selected in ≥60% of subsamples will be retained, in addition to a clinically prespecified core set (age, sex, diabetes duration, baseline HbA_1c_, insulin modality, governorate, BenCGM, BurCGM, SEDM, and PAID-Peds). The final model will be sparse and interpretable; Shapley additive explanations (SHAP) values will be reported to support clinical interpretation of individual predictions.

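### The RCT comparison of sensor-wear days is described without any baseline covariate; naming one or two measured in both arms could add modest precision at little cost

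*Protocol article*

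**What the plan says.** The Outcomes section of Substudy 3 makes the primary outcome continuous: CGM adherence, "defined as mean days per week of sensor wear over the 12-month follow-up". The Data Analysis section gives the between-group comparison for the RCT: t tests, chi-square tests and "mixed effects models with random intercepts for repeated measures". No covariate is named there.

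Baseline variables enter that section in two other roles:
- Exploratory regression: "Multivariable linear and logistic regressions will explore predictors of adherence change".
- Subgroups: "Prespecified subgroup analyses will examine age band (10-13 vs 14-18 years), sex, governorate (Muscat vs others), and insulin modality" (multiple daily injections vs pump).

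Other parts of the article bear on the point:
- The eligibility criteria admit to the RCT only newly diagnosed children who have not yet received CGM.
- Randomization and Blinding specifies simple 1:1 allocation.
- Table 2 schedules demographic characteristics at baseline. It also ticks the "OMNIdiasense score" at baseline and at every later visit, as the source for the row "CGM^a^ adherence (optimizer vs subuser"), and does not separate the arms.
- The Design section gives controls usual care without exposure to the tool.
- The feature-selection section puts age and sex in the model's "clinically prespecified core set (age, sex, diabetes duration" and further items), along with BenCGM, BurCGM, SEDM and PAID-Peds.
- Reporting Guidelines and Dissemination says that a full statistical analysis plan exists and can be requested.

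**The concern.** The programme rests on the idea that information available before dispensing predicts wear. If it does, a comparison of wear in 50 children can use such information to reduce residual variance. In many trials the natural covariate is the baseline value of the outcome. Here it cannot exist, and the article names nothing in its place. Two of the three named methods, the t test and the chi-square test, cannot take a covariate at all.

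Simple randomization gives no design-stage control over prognostic balance, so a chance imbalance in a predictor passes into the unadjusted difference. Table 1 says the RCT is to supply the effect-size estimate for a definitive trial, so the precision of that estimate matters in its own right.

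**Working it through.** **Inputs from the article.** 25 per arm, alpha 0.05, 80% power, 50% optimizer prevalence and odds ratio 0.53 (Substudy 3, Sample Size). The continuous primary outcome is from Outcomes. Sidedness is not stated; two-sided is assumed.

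**Input not in the article.** The correlation rho between a baseline covariate and mean wear days. A range of 0.2 to 0.5 is shown.

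**Step 1: the plan's own figure.** An odds ratio of 0.53 from 50% gives 0.53 / 1.53 = 34.6%. Detecting 50% vs 34.6% with 80% power needs 162 per arm two-sided (127 one-sided); 25 per arm gives 19% power two-sided. On the continuous scale, d = ln(1/0.53) × √3 / π = 0.35, which needs 130 per arm. The stated 25 per arm is not reproduced. By a two-sample t test, 25 per arm has 80% power at d = 0.81. Both effects are carried forward: 0.81 because it matches the claimed power, and 0.35 because it matches the stated odds ratio.

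**Step 2: unadjusted power at 25 per arm.** Noncentral t with 48 df and noncentrality d × √(25/2).
- d = 0.81: 80.0%
- d = 0.35: 22.8%

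**Step 3: adjusted for one covariate.** The variance of the treatment estimate is multiplied by (1 − rho²) × 47/46, where 47/46 is the expected cost of chance imbalance. The df fall to 47, and the noncentrality is divided by the square root of the factor.

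| rho (assumed) | variance factor | power at d = 0.81 | power at d = 0.35 |
|---|---|---|---|
| unadjusted | 1 | 80% | 23% |
| 0 | 1.022 | 79% | 22% |
| 0.2 | 0.96 × 47/46 = 0.981 | 81% | 23% |
| 0.3 | 0.91 × 47/46 = 0.930 | 83% | 24% |
| 0.5 | 0.75 × 47/46 = 0.766 | 89% | 28% |

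Break-even is at rho² = 1 − 46/47 = 0.021. Two covariates with no prognostic value carry a factor of 47/45 and 46 df, and give 78% at d = 0.81, about 2 points below the unadjusted test.

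**Step 4: what rho might be.** Assuming a binormal score and 50% prevalence, an AUROC of 0.70, 0.75 or 0.80 corresponds to rho² of about 0.12, 0.19 or 0.26 for the binary optimizer status. So rho = 0.5 (rho² = 0.25) would need an AUROC near 0.80. The article gives no value for the score, age or sex.

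**Step 5: chance imbalance.** With 25 per arm, the between-arm difference in a baseline covariate has SD √(2/25) = 0.28 covariate SDs, so its 95% range is ±0.55. It shifts the unadjusted estimate by up to 0.55 × 0.3 = 0.17 outcome SD at rho 0.3, or 0.55 × 0.5 = 0.28 at rho 0.5. For comparison, the stated odds ratio corresponds to 0.35 SD.

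**The case against.** **The article may only be silent.** A reader might infer that the plan has decided against adjustment. The text does not support that. It gives no fixed effects for the mixed model, not even arm or visit, and a covariate list is commonly left to a statistical analysis plan. This objection stands. What remains is that the article commits to named tests that cannot be adjusted and does not say which method yields the primary estimate.

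**The score may not exist in controls.** A reader might infer from Table 2 that the baseline OMNIdiasense score is a ready-made covariate. The Design section makes the assessment part of the intervention and keeps controls from exposure to the tool, while Table 2 does not separate the arms. BenCGM, BurCGM, SEDM and PAID-Peds, all in the model's core set, are not listed in Table 2. Scoring controls could therefore mean giving them extra questionnaires. The model is also trained on children who already received CGM, so its predictive value in newly diagnosed children is unknown. This stands, and the score cannot be the default covariate.

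**Age and sex may predict little.** They are in the core set by clinical choice, not because data showed them to be predictive. This also stands; it limits the expected gain, while the loss is capped at about 2 points of power.

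**Little harm is done.** Under randomization the unadjusted difference is unbiased, its interval already reflects chance imbalance, and the authors acknowledge the modest sample size. That is correct, and it makes this a point about precision, not validity.

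**Conclusion.** The point holds in a limited form. As described, the RCT comparison names no baseline covariate, in a setting with no baseline wear value and no stratification. A model with one or two covariates prespecified and measured in both arms is a better choice than a t test, provided the covariates have some prognostic value (rho² above about 0.02 for one covariate).

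The gain is modest and rests on an assumed correlation. At d = 0.81 it is about 1 to 9 points of power for rho 0.2 to 0.5. At the effect matching the stated odds ratio it is from under 1 to about 5 points. These figures assume a two-sided test, exactly 25 per arm and a linear covariate effect.

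A reader might also infer that adjustment would make 25 per arm adequate. It would not: at d = 0.35 and rho 0.5, power is still only 28%. The mismatch between the stated odds ratio and the stated sample size is a separate and larger problem.

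**What to change.** In the Substudy 3 Data Analysis section, state that the primary estimate of mean sensor-wear days per week comes from a single linear or mixed model with arm plus continuous age and sex. Table 2 already schedules demographics at baseline. Report the unadjusted difference as a sensitivity analysis. If the unseen analysis plan already names covariates, the article should carry the same list.

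Use the baseline OMNIdiasense probability as the covariate instead only if two conditions are met. First, the Design section and Table 2 must be reconciled to show that controls are scored by the locked model without disclosure to families or clinicians. Second, the model's inputs must be collected at baseline in both arms.

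For age and sex, the cost is a sentence of text, two degrees of freedom and at worst about 2 points of power. For the score, it is one degree of freedom and at worst about 1 point, plus baseline collection of the model inputs in the 25 controls, possibly including questionnaires not now in the schedule. Recruitment to Substudy 3 is planned for the fourth quarter of 2026, so the wording can be settled before any outcome data exist.
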